### Interventions

Subjects in each group will receive 10 sessions of treatment, each around 20 minutes, during a period of 4 weeks. All treatment, ultrasound delivery, and exercise prescription will be provided by the same licensed and experienced physiotherapist who will be instructed by the researcher about the study protocol.

### Ultrasound application

Therapeutic ultrasound is proposed to deliver energy to deep tissue sites through ultrasonic waves, to produce increases in tissue temperature or non-thermal physiologic changes [19]. Unlike ultrasound for medical imaging (which transmits ultrasonic waves and processes a returning echo to generate an image), therapeutic ultrasound is a one-way energy delivery which utilises a crystal sound head to transmit acoustic waves at 1 or 3 MHz and at amplitude densities between 0.1 and 3 W/cm^2 ^[16,19]. Ultrasonic energy causes soft tissue molecules to vibrate from exposure to the acoustic wave. This increased molecular motion generates frictional heat, thus increasing tissue temperature. Referred to as ultrasound's "thermal effects", this heating is proposed to increase collagen extensibility, increase nerve conduction velocity, alter local vascular perfusion, increase enzymatic activity, alter contractile activity of skeletal muscle, and increase nociceptive threshold [16,19].

While recent systematic reviews of therapeutic ultrasound have failed to identify a dose-response relationship [17], dosage ranges from 0.5 W/cm^2 ^to 3 W/cm^2 ^(spatial average temporal average) have been advocated to minimise adverse effects [20]. Recently published randomised controlled trials which have reported significant benefits of therapeutic ultrasound over placebo ultrasound have used dosages of 1 W/cm^2 ^to 1.5 W/cm^2 ^[18,21].

In the current study, the patients will receive continuous ultrasound using Enraf Nonius Sonoplus 434 operated at a frequency of 1 MHz and intensity of 1.5 W/cm^2 ^(spatial average temporal average). Slow circular movements will be applied by the transducer head over the paravertebral low back region. The duration of ultrasound application will be estimated for each patient using Grey's formula [22]:

For this study, the average local exposure time is planned to be one minute and the effective radiating area of the transducer head is 5 cm^2^. For a patient with an area of low back pain of 40 cm^2^, for example, the required total treatment time is: 1 min × (40 cm^2 ^/5 cm^2^) = 8 minutes.

### Placebo ultrasound

Patients in the placebo ultrasound group will receive the same duration of ultrasound with the apparatus switched on (so that patients will see the lights flashing on the machine) but without any current output. In this way, patients will be blinded for the ultrasound treatment. Success of this blinding, and consequently potential bias, will be evaluated by asking patients at the end of the intervention period if they think that they have received verum or placebo ultrasound.

### Exercise therapy

Exercise therapy is defined as "a series of specific movements with the aim of training or developing the body by a routine practice or as physical training to promote good physical health" [9]. Exercise therapy appears to be slightly effective for decreasing pain and improving function in adults with chronic LBP [9]. Studies on therapeutic exercises often fail to provide details on the specific exercise techniques used and the exact exercise protocol that was prescribed or followed (e.g. dose, timing, intensity) [23]. In our study both groups will receive pamphlets in which all the exercises that are going to be taught during the treatment period will be available in combination with pictures.

This semi-supervised exercise program will start with stretching routines for the lower limbs as well as the lower back. Then strengthening exercises for abdominal muscles and paravertebral muscles of the low back will be added to each session according to the physiotherapist's judgment of the patient's condition. Evidence suggest that lumbar extensor strengthening exercise administered alone or with co-interventions is more effective than no treatment and most passive modalities for improving pain, disability, and other patient-reported outcomes in chronic LBP [23]. The rationale behind choosing this exercise plan was because access to exercise facilities may be limited and patients can easily learn and practice the prescribed exercises at home.

Patients will be asked to perform the exercises on a daily basis (every day). To encourage aerobic activity, patients will be advised to stay active during the day and try to walk for at least 15 minutes before exercising, which can also act as a warm up. In each session the patient will be asked to perform the exercises in front of the therapist to check for correctness. The therapist will then decide whether the patient should be progressed by making the exercises more difficult or increasing the number of repetitions. After completion of treatment sessions patients will be advised to continue staying active and will visit the clinic once a week to check their exercises and continue progression until the follow-up measuring session.

### Avoiding co-interventions

Patients will be requested not to commence new pain medications during the intervention period (from the beginning of treatment sessions until the end of follow-up period) and not to participate in any other exercise or treatment program. Co-interventions, including use of regular pain medication, will be measured during follow-up to evaluate potential bias.

### Outcome measures

Patient's specifications such as age, sex, body mass index, and pain history will be recorded in a demographic questionnaire at the baseline assessment. All primary and secondary outcome measures will be measured by the researcher at baseline, the final treatment session (after 4 weeks), and at a follow-up measurement after 3 months.

Primary outcome measures will be

• Functional disability due to LBP measured by the Functional Rating Index.

• Pain measured on a visual analogue scale (VAS)

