## Methods

### Study design

A single blind randomized controlled trial in which participants with chronic LBP will be randomized to one of two treatment groups:

• Continuous ultrasound + semi-supervised exercise therapy

• Sham ultrasound + semi-supervised exercise therapy

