### Recruitment procedures

Recruitment will take place in two steps: firstly, orthopaedic surgeons from three university hospitals in Tehran, Iran will identify potentially eligible patients and refer them to the research centre at the Rehabilitation Faculty of Tehran University of Medical Sciences. Secondly, the researcher will conduct another screening for inclusion and exclusion criteria and make the final decision regarding eligibility. If eligible, the patient will be provided with oral and written information about the study. After having signed a consent form, patients will be randomized to one of the two treatment groups.

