## Discussion

The fact that there are more than 20 types of treatment for chronic LBP, each of which has multiple subcategories, is a testament that no single approach has yet been able to demonstrate its definitive superiority [34]. For example, exercise therapy is one promising treatment option, but there is still no consensus upon which kind is the most effective [9]. This situation makes it very challenging for clinicians, policy makers, insurers, and patients to make decisions regarding which treatment is the most appropriate for chronic LBP.

Despite the widespread use of therapeutic ultrasound as one of the most popular and commonly used modalities in the field of physiotherapy for LBP patients, there is still limited evidence of its effectiveness. Only a few RCTs have investigated the effect of ultrasound in treating patients with chronic LBP; often with varying methodology qualities and very small sample sizes, and have not been able to provide evidence regarding its usefulness.

The RCT we have described will evaluate the effectiveness of therapeutic ultrasound in addition to exercise therapy in patients with chronic LBP. The advantages of this study would be comparing the ultrasound with placebo ultrasound, which would clarify the value of adding ultrasound to a semi-supervised exercise program. Limited possibilities for double blinding can be a potential limitation to this study. Meanwhile we will evaluate potential bias by asking the patients whether they think they received real or sham ultrasound on the last treatment session. Recruiting a sufficient number of patients will be one of the most challenging elements of this study since it will be conducted without substantial funding.

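### The researcher who measures every outcome is not among those stated to be blinded, although only the separate treating physiotherapist needs to know the allocation

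*Protocol article*

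**What the plan says.** All references are to the protocol article.

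- **Study design** sets the level of blinding: "A single blind randomized controlled trial in which participants with chronic LBP will be randomized to one of two treatment groups".
- **Placebo ultrasound** names the blinded party during treatment, with the sham device switched on but giving no output: "In this way, patients will be blinded for the ultrasound treatment". Patients are later asked which treatment they think they had.
- **Data collection and analysis** adds that the analyses are done without knowledge of allocation.
- **Outcome measures** gives the assessor's role to one person at every visit: "All primary and secondary outcome measures will be measured by the researcher at baseline", then at the last treatment session and at follow-up.
- **Interventions** gives treatment to someone else. Ultrasound and exercise "will be provided by the same licensed and experienced physiotherapist who will be instructed by the researcher about the study protocol".
- **Recruitment procedures** says "After having signed a consent form, patients will be randomized to one of the two treatment groups". Neither this section nor Outcome measures says whether baseline is taken before allocation is known.
- **Randomization** has an uninvolved statistician prepare opaque sealed envelopes. It does not say who opens them.
- **Discussion** concedes: "Limited possibilities for double blinding can be a potential limitation to this study".

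**The concern.** The article names the level of blinding, names patients and analyses as blinded, assigns all measurement to the researcher, and then presents restricted blinding as a limitation. Read together, these statements leave the assessor outside the blinded group. That makes this a stated design choice, and more than a detail lost in condensing a protocol into an article.

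The limitation in the Discussion does not explain the choice. Whoever applies active or sham ultrasound must know which it is; whoever measures the outcome need not. The article already gives these tasks to different people.

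At stake is the credibility of outcomes that depend on the examiner. The Sample size section says the investigators expect ultrasound to do better and uses that expectation to justify a one-sided test. If the assessor shares the expectation and knows the allocation, any influence on a measurement would tend towards the result the test is set up to find.

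**Working it through.** No figure in the article bears directly on this point, so the check sets the sections side by side.

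**1. Who does what, and who is stated to be blind**

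| Role | Person | Section | Stated to be blind? |
|---|---|---|---|
| Receives ultrasound or sham | Patient | Placebo ultrasound | Yes |
| Delivers ultrasound and exercise | One physiotherapist | Interventions | No; has to know |
| Measures all outcomes | The researcher | Outcome measures | Not stated |
| Opens the envelope | Not stated | Randomization | Not stated |
| Analyses the data | Not stated | Data collection and analysis | Yes |

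The third row is the gap. The second row shows that it is avoidable, because the one role that must be unblinded belongs to a different person.

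**2. Which outcomes an unblinded assessor could move**

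| Outcome | What fixes the recorded value | Route for assessor influence |
|---|---|---|
| Functional Rating Index (primary) | The patient selects each item score | Indirect, through administration |
| Pain VAS (primary) | A point on a 100-mm line, apparently marked by the patient | Indirect, through administration |
| Schober flexion and extension (secondary) | Distance between two skin marks, both marking and measuring done by an examiner | Direct |
| Biering-Sorensen holding time (secondary) | How long the patient keeps the position at the examiner's request | Direct, through instruction; the end point is a goniometer reading of more than 5 degrees, which limits reading error |
| EMG frequency slopes and intercepts (secondary) | Computed from the recorded signal in MATLAB | Limited |

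The section on recording surface EMG itself says that endurance time suffers from the patient's motivation and tolerance, and gives this as the reason for using spectral indices. Holding time is nevertheless listed among the quantities to be extracted and analysed.

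**3. Does blinding the assessor change the sample size?**

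Inputs from Sample size: effect size 0.8, one-sided alpha 0.05, power 0.80.

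- Normal approximation: n per arm = 2(1.645 + 0.842)² / 0.8² = 12.37 / 0.64 = 19.3, rounded up to 20.
- t-test solution: 20.03, rounded up to 21 per arm, or 42 in total. This reproduces the article's figure. Power at 21 per arm is 0.817.
- Drop-out of 10%: 42 × 1.1 = 46.2, or 42 / 0.9 = 46.7, against the stated 46.

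None of these inputs concerns who is blinded, so the change leaves sample size and power as they are.

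**The case against.** **The assessor's unblinding is inferred.** No sentence says that the researcher knows the allocation. The researcher instructs the physiotherapist about the protocol, which is not the same as knowing who gets what. Envelope handling and the order of visits are details a condensed article may leave to the full protocol. This stands as a limit on the wording: the point is that the assessor is not stated to be blind. It does not remove the point, because the article itself chose the single-blind label and the Discussion defends it. If the researcher is meant to be blind, both need correcting.

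**The primary outcomes are largely protected.** Patients blinded by a sham score the disability index and appear to score the VAS, and the success of their blinding is checked. This stands, and it places the concern mainly on the secondary outcomes.

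Four stronger readings are tempting, and the documents do not support them:

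- *Only patients are blinded.* The analyses are blinded too.
- *The researcher's eligibility role is itself a source of bias.* Surgeons screen first, and the envelopes are sealed, opaque and prepared by an uninvolved statistician. With allocation concealed, the same person deciding eligibility and later measuring outcomes adds little.
- *The false-positive rate is inflated by a known amount.* With 21 per arm, one-sided alpha 0.05, no true effect and an assumed assessor shift of b SD, the normal approximation Φ(b√(21/2) − 1.645) gives 5% at b = 0, about 9% at 0.1, 16% at 0.2 and 25% at 0.3. Every value of b is an assumption. The documents support none of them for any outcome, least of all for the patient-rated primaries.
- *Blinding the assessor is free.* It needs no new staff, but someone other than the researcher must open envelopes and set the device. The second measurement falls at the last treatment session, so the researcher must be kept apart from treatment.

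**Conclusion.** The point holds in a limited form. Patients and analyses are blinded, the researcher who measures everything is not stated to be, and the limitation in the Discussion does not account for this, since the treating physiotherapist alone needs to know the allocation.

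The exposure is mainly in range of motion and holding time. For the Functional Rating Index and VAS it is indirect. The size of any bias cannot be derived from the documents, so no inflated error rate should be quoted as a finding.

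The conclusion rests on two readings: that the single-blind label together with silence about the assessor means the assessor may know the allocation, and that the researcher and the physiotherapist are different people, as Interventions implies. It does not show that any result would be wrong. It shows an avoidable risk that the existing division of roles allows the trial to close.

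**What to change.** Amend Study design, Randomization and Outcome measures to state that:

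1. the researcher completes eligibility and all baseline measurements before allocation;
2. the treating physiotherapist, not the researcher, opens the next envelope and sets the device;
3. patients are asked not to discuss their treatment with the researcher;
4. the researcher stays unaware of allocation until the data are locked, and records a guess of each patient's allocation at the last visit, matching the check already planned for patients.

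Then describe the trial as participant- and assessor-blinded, and reword the limitation in the Discussion so that it refers to the treating physiotherapist.

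The cost is an envelope handover and keeping the researcher away from treatment sessions, including the one at which the second set of outcomes is taken. No extra staff are needed, and sample size and power do not change.

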### Functional Rating Index

The Functional Rating Index (FRI) is an instrument specifically designed to quantitatively measure the subjective perception of function and pain in the spinal area in a clinical environment. It has shown to also have satisfactory reliability and validity [24,25]. The FRI is a 10-item questionnaire consisting of 5-point Likert scales. The patient ranks his or her perceived disability at the present time by selecting one of the five points of the scale (0 - "no pain or full ability to function"; 4 - "worst possible pain and/or unable to perform this function at all"). The total score is obtained by summing the item scores and expressed as percentage from zero (no disability) to 100% (severe disability).

### Visual analogue scale

A visual analogue scale (VAS) is a commonly used, quick, reliable, and valid means to measure pain intensity in a variety of clinical contexts. This scale is a 100-mm horizontal line, where 0 mm indicates ''No pain'' and 100 mm indicates ''Unbearable pain.''

Secondary outcome measures will be

• Paravertebral muscle fatigue during a Biering-Sorensen test using surface electromyography and analysing the changes in fatigue indices after the treatment.

• Lumbar flexion and extension range of motion using the modified-modified Schober test

Reduced endurance capacity of back extensor muscles has been associated with chronic LBP [26,27]. Electromyography (EMG) spectral indices and their shift towards lower frequencies have been validated as tools to objectively monitor local lumbar back extensor fatigue in both healthy and LBP populations [28,29]. In this study we use EMG indices to evaluate whether the addition of ultrasound to exercise therapy will result in improved endurance outcomes.

### Biering-Sorensen test

The Biering-Sorensen test is a method for evaluating paravertebral muscle fatigue which was first introduced by Hansen and then modified by Biering-Sorensen [26]. In this test the subject will be asked to keep an unsupported prone horizontal position as long as possible, while their legs and hips are fixed to a bed. We will use a two part hydraulic bed in which the section under the upper body can be brought down slowly by pressing on an electronic button. The examiner will then ask the patient to keep his/her horizontal position. During the test, EMG activity of iliocostalis lumborum, multifidus and gluteus maximus will be recorded bilaterally using an 8 channel surface EMG recorder (DATA Log Biometrics Ltd). Surface EMG activity of the dominant side biceps femoris will also be recorded. The eighth channel will be connected to a digital goniometer. The end point of holding time would be when the patient fails from the horizontal position by more than 5 degrees as recorded by a digital goniometer.

### Recording surface EMG activity

Usually, assessment of fatigability in the Biering-Sorensen test is based on measuring endurance time, but this is hampered by subjective qualities such as motivation and tolerance to discomfort or pain. Electromyographic (EMG) spectral index compression toward lower frequencies has been employed to overcome this problem by measuring objectively the back extensor fatigability in isometric endurance contractions [30]. After shaving and cleaning the skin, the following electrodes will be attached:

#### Iliocostalis lumborum and multifidus

The determination of muscle fibre orientation is based on the recommendations of De Foa et al [31].

#### Gluteus maximus

At the midpoint of a line running from the inferior lateral angle of the sacrum to the greater trochanter [32].

#### Biceps femoris

At the midpoint of a line running between the ischial tuberosity and the proximal head of the fibula [32].

The digital goniometer will be positioned on the lumbar region according to the manual instruction of the apparatus. Surface EMG of the isometric activity of these muscles will be recorded during holding time. Holding time, median and mean power frequency slopes and intercepts, as well as the slope of the standard deviation of lumbar angle will be extracted from raw EMG using MATLAB version 7 and analysed by SPSS, version 17.

### Lumbar range of motion

Lumbar flexion and extension range of motion will be measured according to the modified-modified Schober (MMS) method. The MMS test has shown to produce reliable measurements of spinal flexion and extension in patients with LBP (Pearson's r = 0.78 to 0.89 for flexion and 0.69 to 0.91 for extension) compared with use of the double inclinometer technique (Pearson's r = 0.13 to 0.87 for flexion and 0.28 to 0.66 for extension), with less time to obtain the measurement [33].

In this method the two posterior superior iliac spines (PSIS) will be connected with a line on the skin and the middle of the line (first mark) and 15 cm above (second mark) will be marked. As the patient moves into lumbar flexion or extension, the distance between the two marks is measured and subtracted from the 15 cm distance in the neutral position [33].

### Data collection and analysis

An intention-to-treat analysis will be performed. In the case of dropouts and withdrawals, the last recorded values for the main outcome measures will be used in the analysis. We will check if the two groups are similar for the most important demographic characteristics and all outcome measures at baseline. In case of finding any differences we will adjust for them in a regression analysis. Between-group differences in the change of scores of all outcome measures will be analysed using the Statistical Package for the Social Sciences (SPSS) version 17. We will consider whether the data meet parametric or non-parametric conditions. If parametric, ANOVA, independent and paired t-tests will be used and in case of non-parametric conditions we will use Kruskal-Wallis, Mann-Whitney and Wilcoxon signed-rank tests. All analyses will be performed blinded for treatment allocation.

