### Randomization

Opaque, sealed envelopes will be prepared to the total number of patients using a computer generated randomization schedule, with half of the envelopes being allocated to each group ensuring equal number of subjects in each group.

The list and the envelopes will be prepared by a statistician who is not involved with the study prior to commencement of the trial to ensure concealment of patient allocation.

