### Sample size

According to the data of a randomised pilot study which involved 10 patients, the effect size based on the Functional Rating Scale (FRI) was calculated to be 1.83. Since the number of patients in the pilot study was few, we calculated the sample size for the current study using an effect size of 0.8. Considering the results of our previous article [18] and the results obtained from the pilot study we expect ultrasound to be more effective and have chosen a one-sided test to calculate the sample size. Assuming alpha and power to be 0.05 and 0.8, in a one-tailed test the total sample size needed is 42 (21 patients in each group). Accounting for 10% drop-out, the total number of patients required is 46 (23 patients in each group).

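### Carrying the last value forward shrinks a real effect when early dropout is equal between arms, and biases the comparison in either direction when it is unequal

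*Protocol article*

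**What the plan says.** The Data collection and analysis section commits to intention-to-treat ("An intention-to-treat analysis will be performed") and then fixes how gaps are filled: "In the case of dropouts and withdrawals, the last recorded values for the main outcome measures will be used in the analysis". The main outcome measures are the two primary ones, FRI and VAS. The quantity compared is change: "Between-group differences in the change of scores of all outcome measures will be analysed".

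Under Outcome measures there are three assessments: baseline, the last treatment session at 4 weeks, and a follow-up. That section puts the follow-up at 3 months; the Abstract puts it at one month. Under Exercise therapy, both arms follow the same semi-supervised programme, described as having a small benefit on pain and function, with weekly checks and progression up to the follow-up assessment.

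The Sample size section allows for losses: "Accounting for 10% drop-out, the total number of patients required is 46 (23 patients in each group".

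**The concern.** With no outcome between baseline and week 4, anyone who stops during treatment has only a baseline score. Carrying it forward gives a change of exactly zero at both later assessments. Anyone who stops after week 4 keeps the week-4 score while the other patients continue to exercise. In a trial where both arms are expected to improve, neither value is neutral.

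Two things are at stake. A real benefit of ultrasound is diluted by patients entered as unchanged. And if the arms lose different numbers, the arm with more losses looks worse for that reason alone. With 23 patients per arm, a difference of a few patients is enough to matter, and the sample size was planned on a one-sided test in favour of ultrasound.

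**Working it through.** **Inputs from the protocol.** 23 per arm, allocated 1:1 (Randomization: "with half of the envelopes being allocated to each group ensuring equal number of subjects in each group"); standardised effect 0.8 ("we calculated the sample size for the current study using an effect size of 0.8"); one-sided alpha 0.05 and power 0.80; 10% dropout, that is 0.10 × 46 = 4.6, or 4 to 5 patients.

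**Assumptions, because the protocol gives no figures.** Common improvement *m* in both arms of 0.5 to 1.5 SD; SD of change 1; all losses before week 4; leaving unrelated to response within each arm.

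**The plan's own figure.** The protocol states "Assuming alpha and power to be 0.05 and 0.8, in a one-tailed test the total sample size needed is 42 (21 patients in each group". The normal approximation gives 20 per arm; the exact one-sided noncentral-t calculation gives 21 per arm (power 0.817), so 42 in total. For dropout, 42 × 1.1 = 46.2 and 42/0.9 = 46.7. The planned 46 is reproduced to within a patient.

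**Expected estimate under carry-forward.** Let dU and dS be the shares lost before week 4 in the ultrasound and sham arms, and δ the true effect:

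E = (1 − dU)(m + δ) − (1 − dS)m = δ(1 − dU) + m(dS − dU)

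*Equal loss, 10% in each arm.* The second term vanishes. For δ = 0, E = 0. For δ = 0.80, E = 0.80 × 0.90 = 0.72.

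*Unequal loss, δ = 0.* Bias = m × (difference in number lost)/23:

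| Early losses, ultrasound v sham | m = 0.5 SD | m = 1.5 SD |
|---|---|---|
| 2 v 3 | 0.5 × 1/23 = 0.02 | 1.5 × 1/23 = 0.07 |
| 1 v 4 | 0.5 × 3/23 = 0.07 | 1.5 × 3/23 = 0.20 |
| 0 v 5 | 0.5 × 5/23 = 0.11 | 1.5 × 5/23 = 0.33 |

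Reversing a split reverses the sign.

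**Simulation** (23 per arm, 40,000 runs, one-sided 0.05). The estimates agree with the formula. Ranges run from m = 0.5 to m = 1.5.

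| Loss, ultrasound / sham | δ | Estimate | Rejection rate |
|---|---|---|---|
| 10% / 10% | 0 | 0 | about 0.05 |
| 10% / 10% | 0.80 | 0.72 | 0.78 to 0.69 (0.74 at m = 1.0) |
| 5% / 15% | 0 | +0.05 to +0.15 | 0.073 to 0.124 |
| 5% / 15% | 0.80 | 0.81 to 0.91 | about 0.87 to 0.88 |
| 15% / 5% | 0 | −0.05 to −0.15 | below 0.05 |
| 15% / 5% | 0.80 | 0.63 to 0.53 | 0.67 to 0.47 |
| 0% / 20% | 0 | +0.10 to +0.30 | 0.10 to 0.25 |

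A completers' t-test, which is unbiased here because dropout is random within arms, gives 0.80 with power about 0.81 and a type I error of about 0.05.

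**Standard error.** Treating filled values as observed raises the apparent sample size, but the zeros add spread: the variance per arm is (1 − d) + d(1 − d)M², where M is that arm's mean improvement. With 10% loss in each arm and δ = 0, the simulated standard errors are 0.281, 0.292 and 0.308 for m = 0.5, 1.0 and 1.5, against 0.309 for completers: 9%, 6% and 0% smaller. With δ = 0.80 they are 0.291, 0.307 and 0.327 against about 0.31: 6% smaller, 1% smaller and 5% larger.

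**The case against.** Four points on the other side deserve weight.

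- **The expected loss is small.** With 4 to 5 patients lost and a near-even split, the null bias is 0.02 to 0.07 SD against a target of 0.8. The protocol describes the exercise benefit as slight, so the lower end of the assumed improvement may be the more realistic. Later leavers carry a real week-4 score and are in error only by the change after week 4. All this stands, and it limits the size of the point.
- **Equal loss is conservative.** It leaves a null effect alone and shrinks a real one, so it cannot create a false claim of superiority. True, but it takes back part of the power that the extra patients were meant to protect.
- **Zero may be the right value for some leavers.** A reader might infer that sham patients who leave for lack of relief produce the biases above. The formula does not support that: it assumes leavers would have improved like the rest of their arm. If they leave because they have not improved, zero is close to their true state and little spurious difference arises.
- **A condensed article may leave detail to a fuller plan.** That answers any complaint about missing sensitivity analyses or the handling of secondary outcomes. Naming only the main outcomes in the carry-forward rule does not contradict intention-to-treat. It does not answer the present point, because the article itself fixes carry-forward as the method for FRI and VAS.

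**Conclusion.** The point holds in conditional form and should be acted on. Carry-forward, with this visit schedule and exercise in both arms, can give a wrong answer. Equal early loss of 10% attenuates a true 0.80 SD to 0.72 SD and lowers power to about 0.78 to 0.69. Unequal early loss biases a null comparison by about 0.07 to 0.20 SD (1 v 4) or 0.11 to 0.33 SD (0 v 5). The sign depends on which arm loses more; greater sham loss favours ultrasound and raises the one-sided error.

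These figures rest on an assumed improvement of 0.5 to 1.5 SD, on all losses falling before week 4, and on leaving being unrelated to response within arms.

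Three stronger readings are not supported. Carry-forward does not bias the comparison whatever happens, nor does it always favour ultrasound: nothing in the protocol says which arm will lose more. It does not always understate uncertainty: the standard error is up to about 9% too small when improvement is modest, but the shortfall disappears or reverses when improvement is large. And the sample size is not wrong on this account, since 42 and 46 reproduce.

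**What to change.** Replace carry-forward as the main analysis of FRI and VAS with one of the following:

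- a likelihood-based repeated-measures model on all observed data, with baseline, week 4 and follow-up all as outcomes, baseline means constrained equal between arms, treatment-by-visit effects after baseline, and an unstructured covariance over the three assessments; or
- multiple imputation using arm, baseline and week-4 values, after which the planned comparison of change scores can be kept.

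Both keep every randomised patient in the allocated group, including those with a baseline score only. A model that takes baseline only as a covariate and requires a post-baseline value would drop exactly the patients who cause the problem, so it is not a sufficient repair. Keep carry-forward as a sensitivity analysis.

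Reconcile the follow-up time between the Abstract (one month) and Outcome measures (3 months), since it sets how long a week-4 value would be carried.

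The cost is revised analysis wording and a little more analysis work, with no extra patients or visits. The new analysis relies on dropout depending only on observed data, and patients with only a baseline score will add little information.
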